## Abstract

**Background:**

Greater trochanteric pain syndrome (GTPS) is a painful condition characterised by pain around the greater trochanter usually affecting middle-aged women. The majority of patients will improve with conservative management such as physiotherapy and non-steroidal anti-inflammatory drugs (NSAIDs); however, if this fails then more invasive treatments including corticosteroid injections and surgery may be required. Platelet-rich plasma (PRP) is an autologous blood product, which has a higher concentration of growth factors postulated to provide enhanced healing and anti-inflammatory properties. There have been numerous studies on PRP’s efficacy in musculoskeletal soft tissue conditions with similar pathology to GTPS, with varying results, most promising being in plantar fasciopathy and patellar tendinopathy. Corticosteroids are the established second-line treatment, but do not always work long term. PRP may be a suitable alternative to corticosteroid in GTPS with longer-term effects; however, there are very limited reports. The Hip Injections PRP Vs Placebo (HIPPO) trial aims to assess the ability of PRP to improve symptoms and function in patients with GTPS.

**Methods/design:**

HIPPO is a single-centre, double-blind randomized placebo-controlled study in patients with a radiologically confirmed diagnosis of gluteus medius or minimus tendinopathy with swelling within the tendon insertion with or without bursitis. We aim to randomise 102 patients with GTPS to either the PRP or placebo (normal saline injection) treatment arm. Participants will receive one ultrasound (US) guided PRP/placebo injection into the trochanteric bursa and surrounding gluteus medius/minimus tendons. The primary outcome measure is the International Hip Outcome Tool-12. Secondary outcome measures will include a visual analogue score for pain, the three-level version of the EuroQol five-dimensional questionnaire and the modified Harris Hip Score. Outcomes will be measured at baseline, 3, 6 and 12 months. Participants will have the option at 6 months to have a repeat blinded injection or cross over to PRP. Analyses of primary and secondary outcomes will be made according to the intention-to-treat principle. The trial reporting will comply with Consolidated Standards of Reporting Trials (CONSORT) guidelines.

**Discussion:**

The HIPPO study has been designed to test the hypothesis that PRP is effective in treating GTPS in patients who have failed conservative management and to assess the duration of effect of PRP.

**Trial registration:**

ClinicalTrials.gov, NCT03479190. Registered on 27 March 2018.

**Electronic supplementary material:**

The online version of this article (10.1186/s13063-018-2907-x) contains supplementary material, which is available to authorized users.

## Background

### Overview

Greater trochanteric pain syndrome (GTPS), also known as trochanteric bursitis, can be a debilitating condition characterised by pain around the greater trochanter. Pain increases on walking, squatting or climbing stairs and when lying on the affected side or when crossing one’s legs [1–3]. GTPS was a term adopted by Karpinski et al. in 1985 instead of trochanteric bursitis as patients did not exhibit typical bursitis signs of swelling, heat, crepitus or fluctuation [4]. This notion has been supported by other studies [5] including a study performed by Bird et al. 2001. They evaluated 24 patients using magnetic resonance imaging with the clinical picture of GTPS and found that the majority of patients had gluteus medius tendon pathology with only 2 patients with isolated trochanteric bursal inflammation [1]. Hence, GTPS instead of trochanteric bursitis appears to be the more accurate way of describing the clinical condition, which clearly may have multiple facets in its pathology.

A selection of non-surgical management options is normally recommended, including rest, ice, stretching, heat, strengthening and oral anti-inflammatory drugs. The majority of patients improve with conservative management; however, if this fails then more invasive treatment options may be explored, including shockwave therapy, corticosteroid injections [6–8] and even surgery. Corticosteroid injection is an established second-line treatment for GTPS that has been shown to be efficacious but not necessarily in the long term, as reported by previously published studies [9]. This notion has been supported by numerous reviews of GTPS management [6, 10–12]. Surgery is usually set aside until the condition has become refractory and conservative measures have been exhausted. Reports of PRP use as a novel therapy in GTPS are very limited. A review of treatments for GTPS by Buono et al. stated the following: “as platelet rich plasma (PRP) has been widely used to stimulate biological tendon healing in patients with chronic tendinopathies, futures trends of research and trials should focus on the application and effectiveness of PRP for the management of GTPS” [11].

### Existing knowledge

PRP is an autologous blood product, which has been postulated to promote healing in damaged or inflamed tissues including muscles, ligaments, bones and tendons. Platelets contain a variety of elements including growth factors and cytokines, which are involved in tissue healing. These include, platelet-derived endothelial growth factor (PD-EGF), platelet-derived growth factor (PDGF), transforming growth factor (TGF), insulin-like growth factor (IGF), vascular endothelial growth factor (VEGF) and basic fibroblast growth factor (bFGF). These growth factors are present in the processes of tissue injury, inflammation and repair. Therefore, theoretically the higher the concentration of platelets, the more growth factors there will be present to promote the healing process when administered directly to the area of interest [13].

PRP has been applied in other fields of medicine including regenerative therapies in oral and maxillofacial surgery [14, 15] Over the past decade or so there have been numerous studies of the efficacy of PRP in treating musculoskeletal conditions similar in pathology to GTPS, such as lateral epicondylitis, patellar tendinitis, rotator cuff pathology, Achilles tendinopathy and plantar fasciopathy. This has been collectively reviewed by several authors with reports of mixed efficacy compared to standard treatments for these conditions with the most promise shown in plantar fasciopathy and patellar tendonitis [16–18]. These reviews all mention the lack of evidence to fully support or reject the efficacy of PRP in these conditions, except for Achilles tendinopathy where PRP showed no difference compared with placebo in a randomised study [19, 20]. The healing or regenerative properties of PRP have shown promise in other orthopaedic areas such as cartilage pathology [21].

### Aims

The aim of the trial is to investigate the clinical efficacy of the novel treatment platelet-rich plasma (PRP) in treating patients with GTPS. The clinical efficacy of PRP will be compared against a placebo injection of normal saline.

### Hypothesis

PRP is an effective treatment for greater trochanteric pain syndrome.

### The need for the trial

GTPS can be a painful and debilitating condition, which as a last resort requires surgery especially if it does not respond to conservative treatment. This is clearly a developing field with a lack of published research with on-going studies investigating the efficacy of PRP in GTPS. Our trial differs from the other trials in its design as we will compare PRP with placebo. Our aim is to conduct a well-designed robust trial to establish whether PRP is effective compared to placebo and what the duration of the effect is for patients suffering from GTPS.

## Methods

### Trial design

The trial will be a two-arm, single-centre, double-blind, randomised control trial (RCT). The study will include a two-way comparison between PRP and placebo normal saline injections for treating GTPS. The trial design has been based on our local experience with using PRP in patients with GTPS and an RCT conducted by Monto et al. in 2014 [22] comparing steroid injection with PRP in patients with severe hip bursitis. Add to this, a pilot study by Ribeiro et al. in 2016 [23], which compared the efficacy of PRP against corticosteroid in the treatment of GTPS.

Participants will be identified and referred for inclusion in the study by their main care provider (general practitioner (GP), orthopaedic surgeon, rheumatologist or extended-scope physiotherapy practitioner). They will then be invited for a first interview where eligibility will be assessed, further information about the study will be given and written consent for inclusion obtained. Potential participants will be permitted to reschedule another interview appointment if they need more time to think about whether they wish to participate. Participants will be allocated randomly to either the PRP or normal saline injection treatment arm. They will receive their treatment under sterile conditions under ultrasound guidance by a consultant rheumatologist (IA). The participant will be contacted by phone a week after receiving treatment to monitor for early adverse events. Participants and outcome assessors will be blinded to treatment arm. Participants will be reviewed at baseline, 3, 6 and 12 months with patient-reported outcome measures (PROM) completed at each of these reviews. During the 6 months follow up participants will be given the option of a repeat injection of their original treatment or if they specifically request PRP then we will offer this to them but maintain the blinding of their original treatment. This was a key ethical discussion point in our focus group meeting engaging patient and public involvement in that expecting participants to potentially continue with placebo for a further 6 months while in pain would place a significant burden on them. The trial is expected to last approximately 4 years allowing 18–24 months for recruitment with the remaining time used to complete the follow up period until the last patient recruited.

The feasibility and scientific quality of the trial has been peer-reviewed and approved by the Principal Investigator (PI) and Research and Development team. The ethical approval was granted by Health Research Authority (HRA) England and the trial is listed with the number 198415. The trial protocol will permit its reporting in line with the Consolidated Standards of Reporting Trials (CONSORT) guidelines [24]. [The Standard Protocol Items: Recommendations for Interventional Trials (SPIRIT) checklist is provided as Additional file 1].

## Recruitment

The source of recruitment will be from their main care provider (GP, orthopaedic surgeon, rheumatologist or extended-scope practitioner). Following the first interview and consent to enter the trial, eligibility checks (Table 1) will be repeated for each participant on the day they attend for treatment, to ensure that participants are not randomised in error. The participant will receive confirmation of their inclusion in the trial, which will also be recorded in their medical notes. Their GP will be informed.

**Table 1 Tab1:** Inclusion and exclusion criteria

Inclusion criteria:	
Over 18 years of age	
Symptoms consistent with GTPS present for at least 6 months	
Radiological diagnosis of GTPS using MRI, or ultrasound scan if MRI contraindicated	
Failed conservative management in any other care setting	
Patient is willing and able to provide written informed consent.	
Exclusion criteria:	
Lacks capacity to provide consent	
Has hip joint osteoarthritis demonstrated on a plain radiograph, requiring treatment	
Presence of confounding pathologies on the hip MRI	
Any extensive surgery or deformity of the hip demonstrated on x-ray	
Presence of systemic disorders – coagulopathy, active infection, immune system disorders, peripheral neuropathy, malignancy, unresolved fractures	
Had any surgical treatment specifically targeted at GTPS e.g. bursectomy/ilio-tibial band lengthening	
Pregnancy	
Anti-coagulant therapy e.g. warfarin, rivaroxaban, apixaban, dabigatran	
Haemaglobin < 10 g/dl or platelets < 150,000/ul	
Unable to safely stop anti-platelet/NSAID medications e.g. recent cardiac stenting	
Has lumbar-sacral spine pathology or a recent history of acute hip trauma	
Has a recent history of acute sciatica	
Is not able to attend or comply with treatment or follow up scheduling	
Participates in any other clinical trial	

### Consent

All potential participants will attend a first interview meeting with our research team following referral from their primary care provider (e.g. GP/orthopaedic surgeon/rheumatologist). They should already have received the trial information sheet. We will explain the purpose and nature of the trial again and assess their eligibility. They will be given up to a week to decide whether they wish to be entered into the trial. A second interview will be rescheduled if necessary. Written consent to enter the trial will be obtained. Once the participant has consented, their baseline PROMs will be assessed and recorded.

## Treatment allocation

### Sequence generation

The allocation sequence will be generated randomly using an online computer-generated randomiser (https://sealedenvelope.com/). The participant will be allocated to either the PRP or normal saline arm of the trial. All injections will be performed by the same consultant rheumatologist who will be not involved in the data collection process.

### Allocation concealment

The allocation sequence will be hidden from the PI and outcome assessors. Their allocation will be recorded on a separate database to which the PI/outcome assessors will not have access. Only the treatment administrator (consultant rheumatologist) will have access to this so they know what treatment they are issuing. They and a dedicated research nurse will be guardians of this allocation sequence database to ensure that the patients, PI and outcomes assessors do not have access. Allocation will be revealed once the trial has ended and data analysis begins.

### Allocation implementation

Participants will be enrolled by our research team lead by the PI (AM). They will have been allocated their treatment randomly. Allocations will be held on a secure database which the treatment administrator (consultant rheumatologist (IA)) will have access on the day of their treatment.

### Blinding

All participants will be blinded to the treatment allocation. All treatments will be prepared in another room and the patient will have a screen between them and their hip preventing them from seeing what treatment they are being given. The treatment administrator will not be blinded. Outcome assessors will be blinded.

### Trial treatments

All participants will attend the hospital as a day case. As per Northumbria Healthcare NHS Foundation Trust policies, written consent will be obtained for their procedure, which will be generic to cover both treatment arms. All participants will have 40 ml of blood drawn using an aseptic technique, which will then be taken to another room for 20 min to simulate the centrifuge time for the PRP preparation, regardless of which treatment they are receiving. They will also have a drape obscuring their hip and treatment area from their line of sight. All these measures are to maintain blinding of the participant to treatment allocation. The procedure will take place in sterile conditions to minimise the risk of infection. They will have local anaesthetic infiltrated superficially and deep in the greater trochanter area. Our consultant rheumatologist will then inject either PRP or normal saline under ultrasound guidance into the trochanteric bursa and abductor tendons (2 ml in the abnormal tendon and 2 ml in the bursa). All participants will then be advised to rest for 72 h and will be referred for physiotherapy.

Participants will be randomised into 2 groups:Test: PRP treatment using the SW-PRP system provided by NTL Biologica – 40 ml of the participant’s own blood is added to 6 ml of ACD-A (Anticoagulant Citrate Dextrose Solution, Solution A). This is then placed into the SW-PRP Syringe Device. The vial is centrifuged at 3850 rpm for 7 min. Red blood cell fluid level in the device is optimised and then centrifuged for a further 4 min at 3850 rpm. Platelet-poor plasma is extracted from the device and discarded. The remaining PRP is extracted from the buffy coat layer; 4 ml of PRP is withdrawn and is ready for administration.Placebo: 4 ml of normal 0.9% saline.

### Physiotherapy

The physiotherapy protocol will include stretching exercises, which consist of gluteal, iliotibial band and piriformis stretching. Prone lumbar extension, supine lumbar rotation and cat stretch exercises will also be included. These are accompanied with strengthening exercises such as side-lying leg lift, clam, gluteal kickback and balance exercises. This will be a general standardised physiotherapy regime and will be standardised across our physiotherapy requests. Naturally the physiotherapy that participants receive may vary, such as by the frequency of sessions, and we accept this as a variable that could influence outcome; however, measures will be taken to minimise this as much as possible.

### Measure of harm and adverse events

Participants will be monitored for adverse events at each follow up. One week after their treatment each participant will receive a phone call to monitor early adverse events. Adverse events will be reported in the study publication.

Expected potential adverse events:PainInfectionFailure to relieve/recurrence/progression of symptoms/exacerbation

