### Secondary

The visual analogue score (VAS) for pain, the Modified Harris Hip Score (mHHS) and the three-level version of the EuroQol five-dimensional (EQ-5D 3 L) questionnaire PROM scores will be collected at baseline, 3, 6 and 12 months and will be compared within and between the PRP and normal saline arms (Fig. 1).

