### Statistical analysis

#### Statistician report

The primary outcome of interest is the change from baseline to 12-month follow up in the iHOT-12, comparing the PRP and placebo group. The study will be run as a superiority trial. The cut-off for statistical significance is set at 5% and desired power at 90%, with two-tailed tests applied. Data on change from baseline are also assumed to be parametric and the *t* test will be applied to the data to assess statistical significance.

The minimally clinically important difference (MCID) for the iHOT-12 has been reported by Sansone et al. as 10 (from 100) and the standard deviation for the change in score from baseline as no greater than 21 [25]. Although, there are few previous data on which to base a sample size calculation, Monto et al. compared change from baseline to 12-month follow up in a group of 40 patient with hip bursitis, with steroids and PRP as the interventions being compared. In the PRP group Harris Hip scores increased from 51.7 to 87.4 whilst in the steroid group, scores increased from 50.5 to 58.8 at 12 months [22]. Since the Harris Hip score is also scored from 100, our sample size calculation is based on these figures. We conservatively assume that change in iHOT score from baseline in the placebo group will be no more than in the steroid group reported by Monto et al., and estimate a maximal change of 10. We also estimate that the change in the iHOT score from baseline in the PRP group will be no less than 27. Using these figures, a minimal sample size at follow up of 66 (33 in each group) will be required.

Pilot data obtained by our team suggest that the rate of refusal to participate should be no more than 25% and the dropout rate no more than 35% over 12 months. Refusal rates tend to be low in this patient group given the chronic nature of the condition and the fact that patients will only be approached once conservative management has failed. Thus, we will need to approach 135.4 (rounded up to 136) patients, and recruit 102 patients to achieve our target sample size.

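### Two of the three listed adverse-event categories mix non-response with injection harm: lack of efficacy shares a line with exacerbation, and pain is unqualified

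*Protocol article*

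**What the plan says.** The section Measure of harm and adverse events does three things.

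- It sets the collection times: "Participants will be monitored for adverse events at each follow up", and "One week after their treatment each participant will receive a phone call to monitor early adverse events".
- It names what is expected: "Expected potential adverse events:PainInfectionFailure to relieve/recurrence/progression of symptoms/exacerbation".
- It states the use: "Adverse events will be reported in the study publication".

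The Outcome measures sections make iHOT-12 the primary outcome, with VAS pain, mHHS and EQ-5D as secondary outcomes, at baseline, 3, 6 and 12 months. The post-treatment visits are the same follow-ups at which adverse events are collected. Table 1 requires symptoms consistent with GTPS for at least 6 months. The Statistical analysis section deals only with the PROMs. It gives no adverse-event analysis, no pooled event total and no safety endpoint.

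**The concern.** A harms table should tell the reader what the injection did to people. Whether the hip pain got better is a separate question, and the PROMs already answer it.

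The list blurs the two in two places. Its third line puts exacerbation, which may be an effect of the injection, together with failure to relieve, recurrence and progression, which describe treatment not working. Its first line is pain with no qualifier, in a population recruited because of pain. At 3, 6 or 12 months that entry cannot separate continuing index pain from pain caused by the procedure. Only infection reads cleanly.

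If PRP is more effective than saline, fewer PRP participants will have entries on the mixed lines for reasons that have nothing to do with safety. A real excess of post-injection pain or exacerbation with PRP would then be hard to see on the lines where it should appear.

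**Working it through.** **Inputs from the Statistician report.** The significance level and power: "The cut-off for statistical significance is set at 5% and desired power at 90%, with two-tailed tests applied". The MCID for iHOT-12 and the SD of change are given "as 10 (from 100) and the standard deviation for the change in score from baseline as no greater than 21". Placebo change is taken as at most 10. For PRP, "the change in the iHOT score from baseline in the PRP group will be no less than 27". The article states these as bounds. They are used here as point values, as its own sample size does.

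**Step 1: confirm the design inputs.** The plan gives no adverse-event figure, so its sample size is the figure to reproduce. The difference is 27 − 10 = 17.

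n per arm = 2 × (1.960 + 1.282)² × 21² / 17² = 2 × 10.51 × 441 / 289 ≈ 32.1, rounded up to 33.

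That gives 66 in total, and 66 / 0.65 = 101.5, rounded up to 102. Both match the article, so 10, 27 and 21 are the design's working values.

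**Step 2: non-response at the design effect.** Assume 12-month change is normal with SD 21. The article sets no threshold for failure to relieve, so two cut-offs are shown.

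| Non-response defined as | Placebo | PRP | Gap |
|---|---|---|---|
| Change below 10 (the MCID) | Φ((10 − 10)/21) = 50.0% | Φ((10 − 27)/21) = 20.9% | 29 points |
| Change of 0 or less | Φ((0 − 10)/21) = 31.7% | Φ((0 − 27)/21) = 9.9% | 22 points |

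With 33 per arm this is about 16.5 v 6.9 participants, or 10.5 v 3.3, before any injection harm is counted.

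**Step 3: what pooling would do.** The article does not specify pooling, so this step is conditional. Let f be the non-response rate from Step 2 and h an assumed true injection-harm rate, independent of response. The pooled rate is 1 − (1 − f)(1 − h). The values of h are assumptions; the documents give none.

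| Non-response cut-off | Assumed h, PRP v saline | Pooled, PRP v saline |
|---|---|---|
| Below 10 | 25% v 10% | 1 − 0.791 × 0.75 = 41% v 1 − 0.50 × 0.90 = 55% |
| Below 10 | 20% v 10% | 36.7% v 55.0% |
| 0 or less | 20% v 10% | 27.9% v 38.5% |
| Equal efficacy, f = 50% in both arms | 25% v 10% | 62.5% v 55% |

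In the first three rows the order reverses. In the last it does not, but a true excess of 15 points shrinks to 7.5.

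**Step 4: break-even.** PRP harm above which the pooled rate would show PRP as worse: h(PRP) = 1 − (1 − h(saline)) × (1 − f(saline)) / (1 − f(PRP)).

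With saline harm at 10%:
- Cut-off below 10: 1 − 0.90 × 0.500 / 0.791 = 43%.
- Cut-off 0 or less: 1 − 0.90 × 0.683 / 0.901 = 32%.

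For saline harm from 5% to 20%, break-even runs from 40% to 49% (below 10) or from 28% to 39% (0 or less).

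**The case against.** A reader might infer that the harms comparison will act as a second efficacy reading and make PRP look safer than saline even when its injection harms are higher. The documents do not support that as a statement about this trial. The article plans no pooled count, no between-arm harms test and no safety endpoint. It says only that events will be monitored and reported. The reversal in Step 3 needs three things together: PRP is superior, its true harm rate is higher, and the categories are collapsed into one rate. The harm rates and their independence from response are assumptions. This part of the objection stands.

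A list of expected events is also not a counting rule. Nothing says that a gain below the MCID generates an adverse-event record, so the gaps in Step 2 show the possible size of the mixing and do not forecast what will be recorded. That stands too.

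The article is a condensed document and commits to CONSORT reporting. Case definitions, time windows and tabulation may sit in the full protocol, so their absence here is not held against it.

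The objection does not remove the list itself, which is stated and not merely left out. Reporting by type keeps infection readable but does not rescue the other two lines. One combines exacerbation with non-response, and the other does not say which pain is meant. The one-week call helps to time procedural pain, but the pain item is not tied to it.

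**Conclusion.** The point holds in a limited form. As written, two of the three listed categories mix non-response with possible injection harm. On the design's own figures, and assuming normal change scores, non-response alone would differ between arms by about 22 to 29 points in favour of PRP, depending on the cut-off. If the categories were also pooled, a true excess of harm with PRP could be diluted, or reversed if PRP is effective. That second step rests on assumed harm rates and on an analysis that the article does not specify.

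The primary analysis and the sample size are untouched. What is at stake is whether the harms report can be interpreted. This is a cheap improvement and not a threat to the trial's main conclusion.

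**What to change.** In Measure of harm and adverse events, and on the matching form:

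- Take failure to relieve, recurrence and progression out of the adverse-event list and report them as lack of efficacy through iHOT-12, VAS pain and mHHS, which are already collected.
- List exacerbation on its own line.
- Replace the unqualified pain item with post-injection pain, meaning new pain or pain worsened from baseline, with the existing one-week call as its time point.
- Keep infection as it is.
- State that adverse events will be reported by type and by arm.

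The cost is a change of wording and of the form, with no extra visit, no extra data and no effect on sample size. The small downside is that staff must separate continuing index pain from post-injection pain. The article says that the trial is already running, so the sooner the list changes, the more events can be classified as they occur.
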